### Participants

This study is a collaboration between Massey University and the Waitemata District Health Board (WDHB), New Zealand. Caregivers of children who meet the criteria for the study will be approached in the first instance by the WDHB Developmental Coordinators.

We calculated that 42 participants (a minimum of 34 participants, and allowing for a 20-% potential dropout rate) would be required for each arm of the trial to demonstrate a clinically significant difference at 80 % power and 5 % statistical significance. Power calculations were based on a 17-unit difference between supplemented groups and placebo in change from baseline to endpoint on the Social Responsiveness Scale (SRS) total score [62], on a mean SRS and standard deviation of 105 and 24.7 units in untreated children with ASD, respectively (from our 2015 pilot study, unpublished). The sample size was calculated using the formula below [63]:$$ N= 2{\alpha}^2K/{\left({\mu}_2\hbox{-} {\mu}_1\right)}^2 $$

where *N* is the sample size required per group, *α* is the SD, K is the constant (7.9 denotes 80 % power and 5 % significance), and (*μ*_2 −_*μ*_1_) is the difference in SRS total score between groups.

To ensure that the study is adequately powered, a blinded interim analysis at >50 % of the initially planned enrolment will be performed by an independent third party to estimate the variance for potential sample size increase.

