### Hypotheses

Both vitamin D and omega-3 status, defined as omega-3 index (red blood cell (RBC) DHA + eicosapentaenoic acid (EPA)), will be low in children with ASD at baseline (25(OH)D <75 nmol/L [59] and omega-3 index of approximately 4–6 % [60, 61])Improving either vitamin D or omega-3 status with supplementation will reduce the severity of ASD symptoms in children with ASDCombined vitamin D and n-3 LCPUFA supplementation will be more effective than either supplement alone or placebo in reducing the severity of ASD symptoms in children with ASD

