Baseline characteristics of participants will be compared among groups using analysis of variance (ANOVA) for parametric data and the Kruskal-Wallis test for non-parametric data. The primary analysis, comparing the effects of treatment on symptoms of autism over 12 months, will be conducted using a generalised linear mixed-models procedure. Treatments and time will be included as fixed effects and the interactions between interventions and time will be tested. If significant main effects or interaction effects are observed, post-hoc analysis with Bonferroni adjustments will be performed. Potential confounding factors and effect modifiers (e.g. baseline 25(OH)D and RBC fatty acids, symptoms of autism at baseline, age and gender) will be investigated within the model. Logistic regression will be used to test the multiplicative interaction. Rothman’s synergy index, which would be equal to unity under additivity, and less than unity when suggesting antagonism, will be utilised to examine the postulated interaction effect of vitamin D and omega-3 LCPUFAs on core symptoms of ASD.

The secondary analysis, comparing the effects of treatment on gastrointestinal symptoms over 12 months, will be conducted using the same procedure. Potential confounding factors and effect modifiers (e.g. baseline diagnosis of any gastrointestinal symptoms and medication/supplement use) will be investigated within the model.

Differences between participants who complete and withdraw from the trial will be analysed using an independent *t* test or the Mann–Whitney test for continuous variables (e.g. age) and chi-square for categorical variables (e.g. gender).

Associations between severity of ASD symptoms and nutritional status (specifically, vitamin D, RBC fatty acids, iron and vitamin B_12_) at baseline will be assessed using regression analysis. The information will be used to assess treatment response according to tertiles of nutritional status showing significant relationship with severity of ASD.

Both intention-to-treat and per-protocol analyses will be utilised, though the primary method of analysis will be intention-to-treat. Statistical significance will be based on two-tailed tests with *P* <0.05 considered significant.

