## Discussion

ASD is a life-long, disabling condition that is associated with deficits in social-communicative functioning, stereotypic behaviour and many behavioural and medical conditions including gastrointestinal symptoms [1, 2, 5–7]. The main purpose of this study is to measure the effect of vitamin D, n-3 LCPUFAs or a combination of both on the symptoms of ASD in affected children. There is a widespread interest in the mechanistic role of vitamin D and n-3 LCPUFAs in brain development and function, with some supportive clinical and epidemiologic studies. However, the effect of supplementing these nutrients on ASD pathogenesis and progression is not known. We anticipate that this trial will provide important insights into this causality of reported associations. As far as we are aware, no other randomised, double-blind, placebo-controlled trial has investigated the effects of vitamin D on symptoms of ASD, and the few trials that have been conducted with n-3 LCPUFAs [38–41] have been limited by small samples sizes and short trial duration and have shown conflicting results.

The strength of this project lies in its design: part 1 has been designed to provide insight into the nutritional status of children with ASD in New Zealand. Part 2 has been designed using a ‘Criterion Standard’ approach (randomised, double-blind, placebo-controlled trial) to investigate the effect of supplementation. The design minimises the effect of potential confounding factors by correcting some nutritional deficiencies prior to the trial entry and taking into account the effect of confounders and covariates on ASD symptoms over time. Our sample size and trial duration will also ensure an adequate power to detect clinically and statistically significant results.

If this trial is able to identify nutritional interventions that can make even a small difference to the lives of children with ASD by reducing their symptoms, the benefits will be considerable in terms of social and emotional well-being and educational achievements. Furthermore, it will also reduce the emotional, physical and financial strains among families or caregivers of autistic children and the wider societal networks. The potential benefits of the current study go beyond New Zealand and will affect all regions where ASD exists, and both vitamin D and omega-3 status below the optimal level is highly prevalent – the general trend of the most regions worldwide.

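### The stated 80 % power is for one unadjusted comparison with placebo; the Bonferroni follow-up has about 55–67 % per pair, and the combination-versus-single and interaction questions were not sized

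*Protocol article*

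**What the plan says.** **Sample size (Participants).** The plan needs at least 34 evaluable children per arm, raised to 42 for 20 % dropout. It says this number "would be required for each arm of the trial to demonstrate a clinically significant difference". The target is a "17-unit difference between supplemented groups and placebo in change from baseline to endpoint" on the SRS total score. The spread comes from a pilot with a "mean SRS and standard deviation of 105 and 24.7 units in untreated children with ASD". The formula is N = 2·SD²·K/(difference)², where "7.9 denotes 80 % power and 5 % significance". A blinded interim look may re-estimate the variance.

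**Analysis (Data handling and statistical analysis).** The primary analysis is a mixed model with treatment, time and their interactions. If a main or interaction effect is significant, "post-hoc analysis with Bonferroni adjustments will be performed". The comparisons that enter the adjustment are not listed. "Statistical significance will be based on two-tailed tests" at 0.05.

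**Hypotheses.** The third hypothesis is that the combination "will be more effective than either supplement alone or placebo in reducing the severity of ASD symptoms".

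**Discussion.** The article states, without qualification: "Our sample size and trial duration will also ensure an adequate power".

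**The concern.** The sample size and the follow-up tests use different significance levels. The constant 7.9 belongs to one comparison at 5 %, whereas the step that says which supplement differs from placebo divides the 5 % by the number of comparisons. The 80 % therefore does not carry over to that step.

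A separate gap concerns the third hypothesis. Beating each single supplement, or showing an interaction, needs its own assumed difference, and the Participants section gives only a difference from placebo.

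A reader who takes the 80 % and the Discussion statement at face value would read a non-significant post-hoc comparison as fair evidence of no effect. The risk is greatest for the combination question, where the trial can detect only large differences.

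**Working it through.** **Inputs.** From Participants: difference 17, SD 24.7 (used for change, as the article does), 34 evaluable per arm, K = 7.9. From the analysis section: two-sided 5 %, Bonferroni. Assumed, because the article does not say: a post-hoc family of either six pairs (all pairs of four arms) or three (each active arm against placebo).

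**The plan's own figure.** N = 2 × 24.7² × 7.9 / 17² = 33.4, so 34. For dropout, 33.4 / 0.8 = 41.7, so 42. Power at 34 per arm and 5 % is 81.0 % by the normal formula and 79.9 % by a two-sample t test. The stated figure is reproduced.

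**Bonferroni pairs.** The standard error of a difference is 24.7 × √(2/34) = 5.99, and 17 / 5.99 = 2.84. Normal power is Φ(2.84 − critical value).

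| Family | Level per test | Critical z | Normal | Two-sample t |
|---|---|---|---|---|
| 1 (as sized) | 0.05 | 1.96 | 81 % | 80 % |
| 3 against placebo | 0.0167 | 2.39 | 67 % | 65 % |
| 6 pairs | 0.0083 | 2.64 | 58 % | 55 % |

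Pooling the error over four arms gives 56 % for six pairs and 66 % for three. If all 42 per arm were evaluable, the figures would be 67–70 % and 76–78 %. The smallest pair difference with 80 % power at 34 per arm is 16.8 units unadjusted, 19.4 for three comparisons and 20.8 for six (normal).

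**Dependence on the SD.** With equal SDs at both visits, the SD of change is 24.7 × √(2(1 − r)), which equals 24.7 only if r = 0.5. The article gives no correlation. Six-pair power, t to normal:

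- r = 0.3: SD 29.2, 38–41 %
- r = 0.5: SD 24.7, 55–58 %
- r = 0.7: SD 19.1, 82–85 %

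**Interaction.** The standard error of the difference of differences is 24.7 × √(4/34) = 8.47. For 17 units, z = 2.01 and power is Φ(2.01 − 1.96) = 52 %. For 8.5 units it is 17 %. The size with 80 % power is 8.47 × (1.96 + 0.84) = 23.7 units.

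**Combination against the single supplements.** If the combination adds 8.5 units over one single supplement, that contrast has 29 % power unadjusted and 11 % with six pairs (normal). If it adds a further 17 units over each, power to beat both is 69 % unadjusted and 40 % with six-pair Bonferroni (simulation, pooled error; the normal version gives 70 % and 42 %).

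**Tests that are not Bonferroni pairs.**

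- Overall 3-df test of change at 5 %, all three active arms 17 above placebo: noncentrality 34 × (12.75² + 3 × 4.25²) / 24.7² = 12.08 on 3 and 132 df, power 83 %.
- Factorial margin, 68 against 68: standard error 24.7 × √(2/68) = 4.24. A 17-unit additive effect has Φ(4.01 − 1.96) = 98 %. If all active arms are equal, the margin is 17 − 8.5 = 8.5 units and power is 52 %.

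**The case against.** The strongest reply is that Bonferroni enters only after the primary model has shown an effect, so 55 % is not the power of the primary analysis. That stands: the overall test has about 83 % if all active arms gain 17, and an additive factorial margin has about 98 %. Even under six-pair Bonferroni, the chance that at least one active arm beats placebo is about 80 % in that scenario. But the overall test does not show which supplement works or whether the combination is better, and those are what the second and third hypotheses ask.

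The six-pair family is also not in the article. Listing the family may be left to a statistical analysis plan, so a range is the fair statement.

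The SD is uncertain in both directions. The model may also include baseline symptoms, which would raise power. At r = 0.5 the adjusted SD would be 24.7 × √0.75 = 21.4, giving about 71 % for six pairs (t) and Φ(17/5.19 − 2.39) = 81 % for three. The sizing itself does not use that adjustment. The interim variance re-estimate could enlarge the trial, but it addresses neither multiplicity nor the unsized contrasts.

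Three stronger readings are tempting and not supported:

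- **The combination hypothesis has no sizing at all.** The target between supplemented groups and placebo can include combination against placebo. The gap is combination against each single supplement, and the interaction.
- **Giving every active arm the same 17 units leaves the third hypothesis nothing to find.** The 17 units is a sizing target against placebo, not a statement that the three effects are equal.
- **The Discussion claims adequate power for the combination.** It makes a general statement that does not mention the combination.

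**Conclusion.** The concern holds in limited form. The arithmetic in Participants is correct, but its 80 % describes one unadjusted comparison of a supplemented arm with placebo. On the same inputs, a given pair in the Bonferroni follow-up has about 55–58 % (six pairs) to 65–67 % (three). A reader might infer that the trial as a whole has only 55 % power. The documents do not support that, because the family is not stated and the primary test is the model.

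The figures assume 34 evaluable per arm, 24.7 as the SD of change and no baseline adjustment; a correlation of 0.7 instead of 0.5 would bring six-pair power above 80 %.

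Independently of the family, combination-versus-single and interaction contrasts were not sized. At an undivided 5 % and the stated SD, only an interaction of about 23.7 units reaches 80 %. The unqualified adequacy statement therefore goes further than the calculation behind it.

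**What to change.** - **Participants:** state that 80 % applies to a single unadjusted comparison with placebo. Name the post-hoc family and give its power (55–67 %, depending on the family), with the assumption that 24.7 is the SD of change (r = 0.5) and the range over other correlations.
- **Participants:** state that the combination-versus-single and interaction contrasts were not sized. Give 52 % for a 17-unit interaction and 23.7 units for 80 %.
- **Discussion:** qualify the general adequacy statement to match.

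The cost is wording and a less favourable stated power; no extra children are needed.

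Testing the second hypothesis on the factorial margins is an option, not a required correction. It gives about 98 % for an additive 17-unit effect but about 52 % if all active arms are equal. If it is chosen, each supplement's simple effect against placebo should be reported alongside.

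### The sample size is stated for change in SRS but uses the SD of a single SRS score, so 80 % power for the planned change contrast rests on an unstated baseline to 12-month correlation of about 0.5 or more

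*Protocol article*

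**What the plan says.** In the Participants section, the target effect is a "17-unit difference between supplemented groups and placebo in change from baseline to endpoint on the Social Responsiveness Scale (SRS) total score". The SD comes from an unpublished pilot study and rests "on a mean SRS and standard deviation of 105 and 24.7 units in untreated children with ASD". The formula is N = 2 × SD² × K / (difference)², with K explained as "7.9 denotes 80 % power and 5 % significance". Below the formula, the difference is defined as one in SRS total score between groups, and change is no longer mentioned. The result is 42 per arm: "a minimum of 34 participants, and allowing for a 20-% potential dropout rate". The section also plans a blinded interim estimate of the variance, by an independent third party after more than half of planned enrolment, with a possible increase in sample size.

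Table 2 schedules the SRS-2 at baseline and 12 months only. Under Data handling and statistical analysis, the primary analysis is a mixed model with treatment and time as fixed effects and a test of their interaction. Symptoms at baseline are named among the factors to be investigated in the model. They are not a fixed term. Tests are two-sided at 5 %.

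**The concern.** The formula needs the SD of the quantity being compared. An SD reported beside a mean level of 105 describes how far children differ from one another at one time. The SD of change also depends on how strongly a child's 12-month score follows the baseline score, and it can be smaller or larger than 24.7. The section gives neither an SD of change nor a correlation, and it moves from change to total score within one paragraph.

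This matters because the sample size, the 80 % figure and the Discussion's assurance of adequate power all rest on this one input. If the interim look estimates the variance of the raw score, the mismatch carries over into any re-estimation.

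**Working it through.** **Inputs from the protocol article.** Difference 17; SD 24.7; K 7.9; two-sided 5 %; 34 evaluable and 42 enrolled per arm; 20 % dropout; SRS-2 at two visits.

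**Assumptions, not in the document.** The SD is 24.7 at both visits. The baseline to 12-month correlation ρ is unknown and is varied from 0.3 to 0.7.

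**1. Reproducing the plan's figure.** N = 2 × 24.7² × 7.9 / 17² = 9639.4 / 289 = 33.35, rounded up to 34. Dropout: 33.35 / 0.8 = 41.7, rounded up to 42. Both figures reproduce. Two-sample t-test power with 34 per arm and SD 24.7 is 79.9 %.

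**2. What the planned test compares.** With two visits, the treatment-by-time interaction between two arms is (mean change in one arm) − (mean change in the other). Its SD per child is SD(change) = 24.7 × √(2(1 − ρ)). This equals 24.7 only when 2(1 − ρ) = 1, that is, ρ = 0.5. Because N is rounded up to 34, the 80 % threshold is ρ = 0.487 by the normal approximation and about 0.50 by the t-test.

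**3. Adding baseline as a covariate to that model.** In 300 simulated data sets at ρ = 0.2 with 34 per arm, adding the baseline score as a plain covariate to the treatment-by-time model left the contrast unchanged. The SD of the estimate was 7.69 with and without it, against 6.16 for an ANCOVA of the 12-month score. Listing baseline symptoms as a covariate therefore does not change the conclusion.

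**4. Both analyses over a range of ρ.** For the 12-month score adjusted for baseline, SD = 24.7 × √(1 − ρ²), which is never above 24.7. N is from the plan's own formula; power is two-sample t-test power with 34 per arm, for one comparison at 5 %.

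| ρ (assumed) | SD of change | N per arm, change | Power, change | SD, baseline-adjusted | Power, baseline-adjusted |
|---|---|---|---|---|---|
| 0.3 | 29.2 | 46.7 | 66 % | 23.6 | 83 % |
| 0.4 | 27.1 | 40.0 | 72 % | 22.6 | 86 % |
| 0.5 | 24.7 | 33.4 | 80 % | 21.4 | 90 % |
| 0.6 | 22.1 | 26.7 | 88 % | 19.8 | 94 % |
| 0.7 | 19.1 | 20.0 | 95 % | 17.6 | 97 % |

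At ρ = 0 the baseline-adjusted SD is 24.7 and the power 79.9 %, which is the floor. The change contrast has 51 % there. The normal approximation gives values up to about one percentage point higher throughout.

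**The case against.** Four points can be made for the plan.

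- **The formula names the total score.** For a total score, 24.7 is the matching SD. Under randomisation the expected difference in change equals the expected difference at 12 months, so 17 units serves for both. This stands, and it makes the defect an inconsistency between score and change. It does not settle the matter, because the effect is stated as change and the planned test is a change contrast.
- **A blinded variance check is planned.** It is a real safeguard against a wrong SD and limits the consequence. It is incomplete because the text does not say whether the variance is that of the score or of the change.
- **The correlation may well exceed 0.5.** It may, and power would then be above 80 %. A reader might infer from the lower rows that the trial is underpowered. The document does not support that, since every correlation in the table is an assumption.
- **The arithmetic is right.** It is. A reader might also infer a dropout error, because 34 / 0.8 = 42.5 would round up to 43. But 42 follows from the unrounded 33.35 / 0.8, so this is only a matter of rounding.

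A main effect pooled over the factorial margins (68 against 68) would have more room: about 92 % at ρ = 0.3 by the normal approximation, if the 17-unit effect holds without interaction. The section, however, sizes each arm against placebo, so its 80 % must stand for that comparison.

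**Conclusion.** The SD entered belongs to a single SRS score, while the stated effect and the planned treatment-by-time test concern change. For that test, 80 % with 34 per arm requires a correlation of about 0.5 or more, given equal SDs at both visits. Over assumed correlations of 0.3 to 0.7, power runs from 66 % to 95 %. The direction of the error is unknown, so this is a power statement without support and not a demonstrated shortfall. The condition does not attach to the sample size as such: under a baseline-adjusted analysis of the 12-month score, 34 per arm gives about 80 % or more whatever the correlation, provided 24.7 is right for the 12-month score. The plan does not commit to that analysis. All figures are for one two-arm comparison without adjustment for multiplicity.

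**What to change.** Two sections must change together; otherwise the new power statement would again not match the analysis.

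1. In Data handling and statistical analysis, make the primary SRS-2 analysis the 12-month total adjusted for baseline, by ANCOVA or an equivalent mixed model that constrains the baseline means to be equal. Adding baseline as a covariate to the present model is not enough.
2. In Participants, restate the power for that analysis: 24.7 is an upper bound on the SD, and 34 per arm gives about 80 % or more for one unadjusted comparison (83 % at a correlation of 0.3, 90 % at 0.5). Define the difference once, in the same terms.
3. If the change contrast is kept instead, state the SD of change or the assumed correlation with its source, and show the power over 0.3 to 0.7.
4. In either case, say that the blinded interim look estimates the variance of the quantity analysed (the change, or the baseline-adjusted residual) and not that of the raw score.

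The dropout sentence can stay as it is. The cost is a short revision of two sections, with no extra children and no extra visits. The choice of primary analysis should be fixed before unblinding.

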### Inclusion and exclusion criteria

Children will be eligible for this study if they are aged between 2.5 and 8 years, have a medical diagnosis of ASD confirmed by both a developmental paediatrician in accordance with the criteria listed in the *Diagnostic and Statistical Manual of Mental Disorders, version five* (DSM-5) [2], and onset of symptoms after 18 months of age. The lower limit of 2.5 years has been chosen based on the age criteria of the psychological assessment tools, and the upper limit of 8 years has been chosen to avoid the confounding effect of behavioural changes associated with pubertal stage. The caregiver’s proficiency in English is a requirement (due to the nature of outcome assessment tools). Volunteers are excluded if they were diagnosed as having developmental delay since birth.

Additional inclusion criteria for the trial are: liver function within the normal range (albumin 34–48 g/L) and serum 25(OH)D <75 + 10 nmol/L if they enter the trial in winter and <105 nmol/L + 10 nmol/L if they enter the trial in summer. A 10-nmol/L variation was chosen because of the potential assay variability [64]. We have applied two different cut-off points for exclusion because there is a large seasonal variation in serum 25(OH)D concentrations in New Zealand ranging from 30 nmol/L [65] to 44 nmol/L [66].

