**Methods/design:**

Children with ASD living in New Zealand (*n* = 168 children) will be randomised to one of four treatments daily: vitamin D (2000 IU), n-3 LCPUFAs (722 mg DHA), vitamin D (2000 IU) + n-3 LCPUFAs (722 mg DHA) or placebo for 12 months. All researchers, participants and their caregivers will be blinded until the data analysis is completed, and randomisation of the active/placebo capsules and allocation will be fully concealed from all mentioned parties. The primary outcome measures are the change in social-communicative functioning, sensory processing issues and problem behaviours between baseline and 12 months. A secondary outcome measure is the effect on gastrointestinal symptoms. Baseline data will be used to assess and correct basic nutritional deficiencies prior to treatment allocation. For safety measures, serum 25-hydroxyvitamin D 25(OH)D and calcium will be monitored at baseline, 6 and 12 months, and weekly compliance and gastrointestinal symptom diaries will be completed by caregivers throughout the study period.

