**Fig. 1 Fig1:**
[figure not shown]
Schematic diagram of study design. ^1^Blood biomarkers: 25-hydroxyvitamin D (25(OH)D), red blood cell (RBC) fatty acids, calcium, albumin, iron studies, vitamin B_12_, folate, full blood count and vitamin A. Questionnaires: sociodemographics, medical history, eating/mealtime behaviours and food diary. ^2^Questionnaires: sociocommunicative functioning, sensory problems and aberrant behaviours (primary outcomes); gastrointestinal symptoms (secondary outcome), sun exposure and skin colour. Anthropometry: weight and height. ^3^Blood biomarkers: 25(OH)D, RBC fatty acids, calcium and albumin. Questionnaires: sociocommunicative functioning, sensory problems, aberrant behaviours (primary outcomes) and eating/mealtime behaviours and diet quality. Anthropometry: weight and height. ^4^Blood biomarkers: 25(OH)D, calcium and albumin. *Gastrointestinal symptoms (secondary outcome) and medication/supplement use/incidence of adverse events/supplement compliance will be monitored throughout the study period

Stage 1 will provide the opportunity for a comprehensive description of the study population with respect to nutritional status (biochemical indices and dietary intake), demographics and medical history. Stage 2 will demonstrate the efficacy of supplementation with vitamin D, n-3 LCPUFAs or both on reducing ASD symptoms.

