	Nutritional supplements and special dietary regimens. Completed by caregiver
Sun exposure and skin colour	Completed by caregiver
Medication/supplement use/incidence of adverse events and supplement compliance	Diary completed by caregiver
Anthropometry	Weight: Tanita electronic scale; Height: Stadiometre; measured by researcher at Massey University

*25(OH)D* 25-hydroxyvitamin D, *HPLC* high-performance liquid chromatography, *RBC* red blood cell

^a^All blood samples are collected and analysed at the North Shore and Waitakere Hospitals

**Table 2 Tab2:** Schedule of enrolment, intervention, and assessment

	Study period						
	Enrolment		Allocation	Post allocation			
Timepoint	t_−2_	t_−1_	t_0_	t_baseline_	t_6-month_	t_12-month_	w_1–52_
Enrolment:							
Initial eligibility screen	♦						
Informed consent	♦						
Nutritional deficiencies screen		♦					
Allocation			♦				
Interventions:							
Vitamin D				♦	♦	♦	
Omega-3 LCPUFAs				♦	♦	♦	
Vitamin D + omega-3 LCPUFAs				♦	♦	♦	
Placebo				♦	♦	♦	
Assessments:							
Nutritional biomarkers							
Serum 25(OH)D				♦	♦	♦	
RBC fatty acids				♦		♦	
Calcium				♦	♦	♦	
Albumin				♦	♦	♦	
Iron studies				♦			
Vitamin B_12_				♦			
Folate				♦			
Full blood count				♦			
Vitamin A				♦			
Primary outcome							
Social Responsiveness Scale-2				♦		♦	
Sensory Processing Measure				♦		♦	
Aberrant Behaviour Checklist				♦		♦	
Secondary outcome							
Gastrointestinal symptoms				♦		♦	♦
Dietary assessment							
Dietary Index Children’s Eating				♦		♦	
Behavioural Paediatric Feeding Assessment Scale				♦		♦	
4-day food diary				♦			
Nutritional supplements and dietary regimen				♦			
Other assessments							
Sociodemographics				♦			
Medical history				♦			
Sun exposure and skin colour				♦			
Compliance and adverse events diary							♦

*25(OH)D* 25-hydroxyvitamin D, *t* timeline, *w* week, *LCPUFA* long chain polyunsaturated fatty acid

According to the SPIRIT statement: Defining Standard Protocol Items for Clinical Trials

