### Blood sampling and analysis

Children will have their blood samples drawn on three occasions, baseline (stage 1 – screening), 6 months (safety measures) and 12 months (endpoint). Refer to Table 1 for nutritional biomarkers and testing methods. The non-fasted blood samples will be collected under the supervision of paediatric staff and processed at North Shore or Waitakere Hospitals of WDHB laboratory service. Nutritional biomarkers will be assayed from a venous blood sample. These include the following: 25(OH)D, RBC fatty acids, calcium, albumin, iron studies, vitamin B_12_ and folate, full blood count and vitamin A. With the exception of RBC fatty acids and vitamin A, all biomarkers will be analysed at North Shore Hospital. RBC fatty acids will be analysed at the University of Wollongong, NSW, Australia, and vitamin A in a laboratory at Massey University, Auckland, New Zealand.

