### Adverse events

All participants will be recalled at 6 months for a blood test to check for hypervitaminosis D (serum 25(OH)D >225 nmol/L) and hypercalcaemia (serum Ca >2.7 mmol/L). Results will be checked by a third party who is unblinded (but has no involvement in analysis of results). The third party will de-identify blood test results and send them to the trial paediatrician and senior investigator for review and recommendation if the child’s serum 25(OH)D or calcium level is above the safe upper limit. If 25(OH)D concentrations are at or approaching 225 nmol/L, or if hypercalcaemia is present, dose administration will be adjusted.

Compliance and gastrointestinal symptom diaries will be monitored on a weekly basis and all side effects will be recorded in the adverse events log to keep a track of the child’s general health and behavioural reactions. In the case of any adverse events, the child’s health will be monitored more closely for three to four consecutive weeks, and if the adverse event persists, the reports will be referred to the trial paediatrician and senior investigator for further investigation.

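### Serum calcium is measured at screening but is not an entry criterion, so as written a child above the trial's own 2.7 mmol/L limit could be randomised

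*Protocol article*

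**What the plan says.** The relevant statements are spread over several sections of the protocol article.

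- **Inclusion and exclusion criteria.** The laboratory conditions for entering the trial open with "Additional inclusion criteria for the trial are: liver function within the normal range", defined as albumin 34–48 g/L. The only other one is a 25(OH)D ceiling of 75 + 10 nmol/L in winter or 105 + 10 nmol/L in summer.
- **Abstract, Methods/design.** Among the safety measures, 25(OH)D and "calcium will be monitored at baseline, 6 and 12 months".
- **Fig. 1 legend.** The first blood panel includes 25(OH)D and "red blood cell (RBC) fatty acids, calcium, albumin, iron studies".
- **Blood sampling and analysis.** "Children will have their blood samples drawn on three occasions, baseline (stage 1" is how the section begins, and the parenthesis goes on to equate baseline with screening. The other draws are at 6 and 12 months.
- **Pre-intervention preparation, Table 3.** Action before randomisation is specified for vitamin D, iron and vitamin B12 deficiency only.
- **Adverse events.** "All participants will be recalled at 6 months for a blood test to check for hypervitaminosis D" (25(OH)D above 225 nmol/L) and hypercalcaemia (calcium above 2.7 mmol/L). For a value over the limit, a third party is to de-identify the results and "send them to the trial paediatrician and senior investigator for review and recommendation". The stated action for calcium is "or if hypercalcaemia is present, dose administration will be adjusted".
- **Randomisation, blinding and concealed allocation.** The third party issues a treatment code after eligibility is confirmed and consent received.

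**The concern.** The trial monitors two blood values for vitamin D safety. One of them, 25(OH)D, has an upper limit at entry as well as a safety limit on treatment. The other, calcium, has only the on-treatment limit. A result that would change a child's dose at month 6 therefore has no stated bearing on whether dosing starts, although it is already available from the screening sample.

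What is at stake is the safety of an individual child aged 2.5 to 8 years who might begin 2000 IU of vitamin D daily with calcium already raised. The 25(OH)D ceiling cannot stand in for a calcium check, because calcium can be high for other reasons. The intervention section also allows any supplement free of vitamin D and omega-3, so calcium supplements are not barred. Efficacy estimates, type I error and power are unaffected.

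**Working it through.** **1. Is the calcium result available before allocation?** The Fig. 1 legend puts calcium in the first panel, and the blood sampling section identifies baseline with the stage 1 screen. Albumin and 25(OH)D, which are used for entry, come from the same panel. On this reading the value is in hand before a code is issued.

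Table 2 ("Schedule of enrolment, intervention, and assessment") is less clear. It lists baseline calcium under the post-allocation heading, in a different column from the nutritional deficiency screen. With only three draws described, I read this as the same sample. If it were a separate post-allocation test, calcium would not be checked before allocation at all, so the gap remains on either reading.

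**2. Does any stated rule act on a high screening value?**

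| Analyte | Limit at entry | Limit on treatment (6 months) |
|---|---|---|
| 25(OH)D | 75 + 10 = 85 nmol/L (winter), 105 + 10 = 115 nmol/L (summer) | 225 nmol/L |
| Albumin | 34–48 g/L | none stated |
| Calcium | none stated | 2.7 mmol/L |

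Table 3 covers low values only. The screening feedback form described under Dissemination of results lists iron studies, vitamin B12, folate and full blood count among the blood results, not calcium. No section attaches a consequence to a high screening calcium.

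**3. How many children could this concern?** The planned total is 4 × 42 = 168, with 2 × 42 = 84 (50%) in the two vitamin D arms. The per-arm figure reproduces from the article's formula: 2 × 24.7² × 7.9 / 17² = 33.35, rounded up to 34; 33.35 / 0.8 = 41.7, rounded up to 42. The documents give no frequency of calcium above 2.7 mmol/L, so the range below is assumed.

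| Assumed frequency | Expected among 168 | Expected among 84 on vitamin D | Chance of at least one on vitamin D |
|---|---|---|---|
| 0.1% | 168 × 0.001 = 0.17 | 84 × 0.001 = 0.08 | 1 − 0.999^84 = 8% |
| 1% | 168 × 0.01 = 1.68 | 84 × 0.01 = 0.84 | 1 − 0.99^84 = 57% |

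**4. How long until the next test?** The next scheduled calcium test is at 6 months. Table 3 postpones iron-deficient children by 3 months without retesting, in a row that concerns iron only. If calcium is not repeated either, and the 6 months run from the start of dosing, the interval is 3 + 6 = 9 months. Both conditions are assumptions.

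**5. How large is the dose?** Against the daily upper limits quoted in the article, 2000/2500 = 80% at 1–3 years and 2000/3000 = 67% at 4–8 years.

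**The case against.** The strongest counter-argument is that this is silence in a condensed article. The full protocol, which is not shown, may contain a calcium exclusion or a procedure for abnormal screening results. The abstract already calls baseline calcium a safety measure, the sample is taken under paediatric staff, and a clinician would probably act on a flagged result. The 2.7 mmol/L limit was written for toxicity on treatment, so using it at entry is a design choice that the document does not make. The dose is below the quoted upper limits, diaries are reviewed weekly, persistent adverse events go to the trial paediatrician, and calcium is rechecked at 6 and 12 months. The size of the problem rests on an assumed frequency.

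Much of this stands. A full protocol may close the gap, clinical judgement may catch a case, the other safeguards lower the risk, and the frequency is unknown.

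The argument from silence is weaker than it looks, however. The article does not defer its entry laboratory criteria to another document: it gives them with numeric limits, explains the assay margin and tabulates the pre-entry actions. The treatment code is issued on confirmed eligibility, and calcium is absent from the criteria listed. None of the other safeguards checks calcium before the first dose; the telephone contacts at 1, 3, 6 and 9 months are for morale and compliance. As for the threshold, a level at which the investigators would alter the dose is a reasonable level at which to pause before starting it.

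**Conclusion.** The concern holds. As the article is written, a child whose screening calcium exceeds 2.7 mmol/L meets the listed trial criteria if albumin and 25(OH)D are within limits, and could start 2000 IU of vitamin D daily. It is a minor safety point, worth considering rather than essential, held with medium confidence because the full protocol is not available.

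In all likelihood few or no children are affected. The expected counts, the chance of at least one case and the 9-month interval are illustrations that depend on the stated assumptions; the conclusion needs none of them. It rests on the listed criteria being the ones applied and on the baseline sample being the screening sample, although the second reading of Table 2 does not rescue the plan. Neither the sample size nor the primary analysis changes.

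**What to change.** Add to the additional inclusion criteria that screening serum calcium must not be above 2.7 mmol/L, and have this confirmed before the third party issues the treatment code. Refer any child above the limit to the trial paediatrician, who already reviews out-of-range results at 6 months, to decide between exclusion and delayed entry.

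The cost is one line in the eligibility check. The test is already done, so no extra blood draw is needed, and no sample size input changes. The downside is that a very few children would be excluded or delayed: about 0.2 to 1.7 in 168 under the assumed range, which is negligible for recruitment.
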